## Abstract

Sleep is bi-directionally linked to energy balance. This crossover study design will evaluate the acute effect of a moderate energy deficit (500 kcal) induced by diet, exercise, or mixed (−250 kcal by diet and 250 kcal by exercise) on sleep and the next morning’s appetitive responses. The study sample comprises 24 healthy young adults. The experimental measurements will be conducted in a naturalistic, momentary manner and partly assessed by the participants. The participants will undergo a run-in period in order to stabilize their sleep schedules and provide them with training on the study protocol and measurements. Indirect calorimetry will be used to determine their resting metabolic rate and peak oxygen consumption (VO_2_ peak). Then, they will take part in a control session (CTL), followed by three energy deficit sessions in random order: a diet-induced energy deficit session (DED), an exercise-induced energy deficit session (EED), and a mixed energy deficit session (MED). All experimental sessions will be separated by a one-week washout. The participants’ sleep will be monitored by ambulatory polysomnography, and the next morning’s appetitive response will be evaluated via ad libitum food intake, appetite sensations, and food reward, measured by a food liking and wanting computerized test.

## 1. Introduction

### 1.1. Background and Rationale

A sustained negative energy balance (EB) is essential for weight loss to occur [1,2,3]. While both exercise and dietary restrictions can be used to induce an energy deficit, they do not seem to induce the same adaptive responses for appetite [4]. It has been shown that an energy deficit induced by dietary restrictions alone promotes compensatory appetitive responses that counter-regulate negative EBs by increasing following energy intake [5]. Interestingly, an isocaloric energy deficit (ED) induced by exercise was found to limit this compensatory response [6]. 

Recent studies have shown that altered sleep patterns while undertaking weight loss programs condition the adherence to and the success of the latter [7,8]. More importantly, it appears that sleep disruption affects the control of EB, mainly through an upregulation (≈250 kcal) of energy intake via various pathways, including appetite hormones, cognitive control, and reward mechanisms [9,10]. Furthermore, it was also found that sleep curtailment during caloric restriction undermines fat loss in favor of increased fat-free mass loss [11,12].

Studies carried out on animal models show that a prolonged restriction of food intake in rats induces a deterioration of sleep, marked by an increase in the time spent awake and a shortening of slow-wave sleep [13,14]. In humans, there is a paucity of evidence documenting the effect of moderate caloric restriction (similar to that induced in clinical practice for weight loss purposes) on sleep. However, some studies underlined that large energy restrictions [≈300 kcal/d] and prolonged fasting lead to a drastic drop in nocturnal melatonin secretion (−20%) [15,16,17]. Melatonin is a hormone produced by the pineal gland in the brain in response to darkness and plays a key role in sleep. Indeed, by lowering the core body temperature, increased melatonin secretion during the evening reduces arousal and increases sleep propensity [18]. Thus, a melatonin deficiency has been related to insomnia and sleep disturbances [19]. Furthermore, Karklin et al. (1994) showed during a dietary weight loss intervention in overweight women with a caloric intake of 800 kcal/d, an alteration of sleep marked by an increase in sleep latency and a decrease in the time spent in slow-wave sleep (SWS) [20]. Moreover, observations of bodybuilders during the “cutting” phase of contest preparation also reported poor sleep outcomes. These periods were generally characterized by severe dietary energy restriction [21,22]. While dietary restrictions may alter sleep, exercise seems to have a completely converse effect. This has been extensively studied over the years, revealing an increase in total sleep time, sleep efficiency (SE), slow-wave sleep (SWS), and rapid eye movement sleep (REM), as well as a decrease in wake after sleep onset in response to acute and chronic exercise [23,24]. However, whether or not these effects are maintained during a negative EB state needs to be determined to draw firm conclusions.

### 1.2. Aims

The main objective of this study is to evaluate the acute effect of a moderate energy deficit (500 kcal) induced by diet, exercise, or both (mixed: −250 kcal by diet and 250 kcal by exercise) on the quality and architecture of sleep in healthy young adults. The secondary objectives will be to investigate the effect of the energy deficit modality on (i) next morning appetitive responses ([i_a_] ad libitum food intake, [i_b_] appetite sensations, [i_c_] food reward, (ii) sleepiness, and (iii) fatigue.

## 2. Materials and Methods

### 2.1. Study Setting and Design

The “Exercise and/or Diet induced Iso-Energetic deficit effect on Sleep” (EDIES) is a single-center study with a crossover design in which each participant will be allocated to a randomized sequence of experimental sessions and, hence, acts as his own control. This trial will be conducted in Toulon, France (Toulon University, laboratory impact of physical activity on health [IAPS]), and received approval from an Institutional Review Board (IRB00012476-2023-28-02-235) with all undertaken assessments complying with the principles of the Declaration of Helsinki. The measurements are realized in a naturalistic, momentary manner and partly assessed by the participants in an ecological setting. The inclusion will be launched in March 2023, and a sufficient number of participants is expected to be reached within three months following the first inclusion.

Upon reception of the signed consent, the participants will undergo a run-in week. This will be followed by a control session (CTL), after which energy deficit sessions (diet-induced energy deficit session [DED], exercise-induced energy deficit session [EED], and mixed energy deficit session [MED]) will take place in random order. All experimental sessions (including the CTL) will be held for 28 h and separated by a one-week washout period (Figure 1).

### 2.2. Participants

#### 2.2.1. Sample Size

An a priori analysis was conducted to establish the number of subjects needed to obtain a statistical power of 80%. Based on a repeated-measures design (four within the measures) for our primary outcome of interest (SE), it was found that 24 subjects would be required for the following parameters: alpha = 0.05, effect size f = 0.25 (medium effect), correlation among repeated measures = 0.5, and sphericity correction = 1. 

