### 2.7. Outcomes

#### 2.7.1. Primary Outcome: Sleep Efficiency

SE is defined as the ratio between total sleep time (TST) and total time spent in bed (TBT). It is given as a percentage. SE will be measured objectively during each session (i.e., CTL, DED, EED, MED) using an ambulatory polysomnograph (Sleep Profiler-PSG2, Advances Brain Monitoring, Carlsbad, CA, USA). The device is a portable multi-channel recorder that allows the acquisition of the following: the electroencephalographic (EEG), electrooculographic (EOG) and electromyographic (EMG) signals from three frontopolar channels; the airflow through a nasal cannula and pressure transducer; head movements and position by actigraphy; snoring, with an acoustic microphone; the pulse, using a forehead and finger sensor; the oximetry, using a wireless wrist oximeter; and the thorax and abdomen efforts by respiratory inductive plethysmography. The records will then be extracted through the Sleep Profiler portal. Validated auto-staging will be applied based on the ratios of the power spectral densities and the auto-detection of cortical and micro-arousals, sleep spindles, and ocular activity [40,41,42], which will be reviewed and modified by a sleep expert if needed. 

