#### 2.10.1. Statistical Analysis for Sleep Outcomes

For the sleep outcomes (TST, SOL, SE, WASO, REM, N1, N2, N3, and arousals), the differences between interventions (EED, MED, and DED) will be assessed using a repeated-measures ANOVA by comparing the three interventions as a within-subject factor. If significance is obtained, post hoc pairwise comparison tests with a Tukey HSD correction will be applied. Sleep measures during the interventions will also be compared to the baseline to evaluate the effect of each intervention separately, using paired samples *t*-tests. The effect sizes will be computed to assess the strength of the relationships: Cohen’s d for the *t*-tests and eta^2^ for the main effects.

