## 3. Discussion and Future Perspectives

From an integrative point of view, the literature in physiology argues that there is an interaction between the energy state and sleep in mammalians. It was suggested that during periods of negative energy balance, neuronal populations, being part of the sleep-wake and metabolic pathways, favor arousal instead of sleep for foraging and survival ends [46].

Given that sleep disruption increases energy intake, appetite, and food rewards [47,48], the elaboration of appropriate interventions intended to promote a sustainable negative energy balance while avoiding compensatory behaviors require the establishment of good sleep quality. On the one hand, this study will allow a better understanding of the interaction between the different modalities of energy deficit and sleep. On the other hand, it will provide additional information on the role of sleep in the following compensatory eating behaviors, with an emphasis on appetite sensations and food reward.

Hunger sensations were implicated in the difficulties initiating and maintaining sleep [49]. Previous studies showed that ED, induced by dietary restriction, potentiates these sensations more than exercise ED [4,6]. Therefore, we hypothesize that exercise ED might be more effective in improving the quality of sleep while reducing appetitive compensatory behaviors in the following morning. In previous work, we showed that an intensive single bout of exercise inducing an ED of almost 500 kcal among adolescent girls with obesity succeeded in improving sleep efficiency (+5%) while reducing next-morning energy-dense food consumption [50]. However, this study was limited by the accelerometry-based measure of sleep and the absence of a detailed assessment of the appetitive response. In addition to addressing these shortcomings, the EDIES study will also allow the evaluation of the feasibility of including this pilot protocol in the clinic. 

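### The 80% power in section 2.2.1 belongs to a four-session test of sleep efficiency; the planned ANOVA compares three sessions and has about 74% power at n=24 if f=0.25 refers to those three

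*Protocol article*

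**What the plan says.** Section 2.2.1 (Sample Size) sets out the "number of subjects needed to obtain a statistical power of 80" percent. The design and the resulting number are worded as follows: "repeated-measures design (four within the measures) for our primary outcome of interest (SE), it was found that 24 subjects would be required". The inputs listed there are "alpha = 0.05, effect size f = 0.25 (medium effect), correlation among repeated measures = 0.5, and sphericity correction = 1".

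Section 2.7.1 (Primary Outcome) confirms four recordings: "SE will be measured objectively during each session (i.e., CTL, DED, EED, MED").

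Section 2.10.1 (Statistical Analysis for Sleep Outcomes) lists SE among the sleep outcomes and tests EED, MED and DED with a "repeated-measures ANOVA by comparing the three interventions as a within-subject factor". Each intervention is then compared with baseline by its own paired t-test. Neither section 2.10 nor any other section describes an omnibus test of SE over four sessions. The Friedman fallback in section 2.10 stands in for these same one-way ANOVAs.

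**The concern.** The sample-size section and the analysis section describe different tests of the primary outcome. The first has four levels and includes the contrast between deficit and control. The second has three levels and asks only whether the deficit modalities differ from one another. Going from four levels to three changes the noncentrality parameter, the degrees of freedom and the question being asked, so the power of the first test cannot be carried over to the second.

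What is at stake is how the result is read. A non-significant ANOVA on SE would be reported as coming from a trial with 80% power for that test, and the document contains no calculation that supports this.

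**Working it through.** **Inputs (all from section 2.2.1 unless noted).** Alpha 0.05, f = 0.25, correlation ρ = 0.5, sphericity ε = 1, n = 24. Number of levels m: 4 in section 2.2.1, 3 in section 2.10.1. No dropout allowance is stated, so all 24 are taken as analysed (assumption).

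**Formula.** Within-subject F test with ε = 1: λ = n·m·f²/(1−ρ), df1 = m−1, df2 = (n−1)(m−1). Power is the probability that a noncentral F exceeds the 5% critical value.

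**Step 1: reproduce the plan's figure (m = 4).**
- n = 24: λ = 24 × 4 × 0.0625/0.5 = 12.0; df 3 and 69; power 81.7%.
- n = 23: λ = 11.5; df 3 and 66; power 79.7%.

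The smallest n reaching 80% is 24, as stated. The plan's arithmetic is right for a four-level test.

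**Step 2: the planned test (m = 3), with f = 0.25 taken to describe the three deficit means.**
- n = 24: λ = 24 × 3 × 0.0625/0.5 = 9.0; df 2 and 46; power 74.1% (simulation, 40,000 runs: 74.0%).
- n = 27: λ = 10.125; df 2 and 52; power 79.6%.
- n = 28: λ = 10.5; df 2 and 54; power 81.2%.

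At n = 24, 80% power needs f = 0.267.

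**Step 3: f = 0.25 taken to describe all four session means.** Dropping CTL leaves an effect among the remaining three that depends on where CTL lies. At n = 24 and ρ = 0.5:

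| Pattern of SE means | f among the three deficits | λ | Three-level power |
|---|---|---|---|
| EED up, DED down, MED and CTL midway | 0.289 | 12.0 | 86% |
| Only EED differs from the other three sessions | 0.272 | 10.67 | 81% |
| DED equal to CTL, MED halfway to EED | 0.246 | 8.73 | 73% |
| All three deficits shift equally from CTL | 0 | 0 | 5% |

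**Step 4: the equal-shift case in the paired t-tests.** Means (0, d, d, d) have a standard deviation of d√3/4. Setting this to 0.25 gives d = 0.577 in units of the within-session SD. With ρ = 0.5 the SD of a difference is √(2 × 0.5) = 1, so dz = 0.577. A two-sided paired t-test at 5% with n = 24 has 77% power, for each comparison and without adjustment for making three.

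**Step 5: sensitivity of the 74%.** Assumed ranges, since the document gives only single values: ρ = 0.4 gives 65.7% and ρ = 0.6 gives 83.6%; ε = 0.8 gives 66.9%.

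**Step 6: a single EED versus DED contrast at three-level f = 0.25, n = 24.**
- MED midway: dz = 0.612, power 82%. This is the largest EED–DED difference that f = 0.25 allows.
- MED equal to DED: dz = 0.530, power 70%.

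**The case against.** The strongest counter-argument is that 74% is not a fact about the trial. Section 2.2.1 assigns f = 0.25 to four measures, and moving the same f to three means is a choice that the document does not make. Under the four-mean reading, some plausible patterns leave the three-level test at 81% or 86%. This stands: a reader might infer that the planned ANOVA simply has 74% power, but the documents support that only on the condition that f describes the three deficit means.

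A reader might also infer that the trial would miss a deficit effect common to all three modalities. The documents do not support that either. Section 2.10.1 compares each intervention with CTL, and those tests would have about 77% power each in that case. It remains true that section 2.2.1 sizes the trial on none of them.

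It can further be said that f and ρ are conventional guesses, that moving ρ between 0.4 and 0.6 shifts power by more than the gap at issue, and that the planned test keeps its type I error and is not biased. All of this is correct and limits the seriousness of the point. It does not remove the mismatch, because the plan fixed its inputs and, on those inputs, the stated power describes a test that is not run.

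Deferring the matter to a separate analysis plan does not answer it: both tests are stated in this document and they differ.

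**Conclusion.** The point holds in a conditional form. The 80% in section 2.2.1 is correctly calculated for a four-level test of SE, but section 2.10.1 plans a three-level ANOVA, so the figure does not apply to the planned omnibus test.

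- If f = 0.25 refers to the three deficit sessions, with ρ = 0.5, ε = 1 and 24 analysed, power is 74%, about 6 points below target and four participants short of the 28 needed.
- If f = 0.25 refers to all four sessions, three-level power has no single value. In the patterns examined it runs from 5% to 86%.

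This is an error in the stated justification, not in the validity of the test. It also gives no ground for replacing the omnibus test with EED versus DED as the sole primary comparison. The statement in section 3 that "we hypothesize that exercise ED might be more effective in improving the quality of sleep" is a tentative discussion hypothesis, whereas the main objective in section 1.2 covers diet, exercise and mixed deficits.

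**What to change.** Reconcile sections 2.2.1 and 2.10.1. In section 2.2.1, state that the three-level ANOVA of SE over EED, MED and DED has about 74% power at f = 0.25 with n = 24 (alpha 0.05, correlation 0.5, sphericity 1), and say explicitly that f describes the three deficit means. If f is instead meant for four means, say so and give the assumed pattern of means, because three-level power cannot be stated without it.

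No extra participants are needed and the planned test does not change. The cost is a sentence or two and a slightly less favourable stated power.

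An EED versus DED contrast may be mentioned as an option at most. Its 82% should then be labelled as the maximum at f = 0.25 (MED midway), with 70% if MED equals DED. Adding CTL to a four-level ANOVA would recover 81.7% on paper, but section 2.1 always places CTL first and outside the randomisation, so that comparison would be confounded with session order.

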#### 2.2.2. Recruitment

The participants will be recruited from a pool of college students through flyers and university e-mail. Then, interested individuals will first be reached by video conferencing to conduct a screening and brief them on the experimental protocol of the study and measurements. Afterward, selected individuals will be invited to a laboratory meeting and informed of all research protocols and details. In light of the information sheet, the first author ([name]) will request written consent from those willing to take part in the study.

#### 2.2.3. Eligibility Criteria

Participants meeting the following criteria will be eligible for the study: (1) be a male; (2) be aged between 19 and 24 years (inclusive); (3) be normal-weighted (BMI: 18.5 to 25 kg/m^2^); (4) have a moderate level of physical activity (i.e., no more than 3 intense exercise sessions per week); and (5) be able to read and understand the French language. 

The non-inclusion criteria are as follows: (1) being involved in another research protocol during the inclusion period; (2) having a specific diet; and (3) having a medical history and medication not compatible with the study (e.g., corticosteroids, sleeping pills), or any other chronic illnesses or injuries that may interfere with the subject’s ability to perform the exercises or that modifies their sleep and eating behaviors; and (4) shift work/severe jet lag.

All diagnosed sleep disorders and/or pathologies will be considered exclusion criteria. All recruited participants will be screened for obstructive sleep apnea syndrome (OSA) using the Berlin questionnaire [25] and the polysomnographic recording of the habituation night (i.e., apnea/hypopnea index > 5 events/hour).

### 2.3. Randomization

#### 2.3.1. Sequence Generation

Upon reception of the signed consent, the participants will be subjected to a random allocation through a computer-generated list (created with “randomization.com”) (Kim and Shin, 2014). According to our within-subjects design, random permutations of interventions will be computed. Thus, each subject can be allocated to a specific order of interventions (any combination of EED, MED, or DED). The sequence allocation will be generated by the study’s statistician and provided to the investigators conducting the assessments. This document will be securely stored and password-protected on the University of Toulon’s online servers and only shared with the team members directly engaged in the study’s protocol.

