#### 2.5.2. Energy Deficit Sessions

All experimental sessions will be conducted similarly to the CTL session. As explained above, the sessions’ order will be randomized and counterbalanced. All meals will be taken at the same time, similar to the CTL session. All measurements will also be organized in the same way, and the participants will be asked to maintain the same level of physical activity as in the CTL session during the 3 experimental sessions, with no structured exercise during and 48 h before the start of each session. Physical activity will again be monitored by accelerometry. Thus, the only difference will be the energy deficit of 500 kcal, induced by the energy balance assessed during the CTL session. Energy deficits will be induced by 3 modalities corresponding to the 3 energy deficit sessions:DED session: 500 kcal dietary deficit (−250 kcal on breakfast and −250 kcal on lunch);EED session: 500 kcal deficit, induced by two exercise bouts (−250 kcal after breakfast and −250 kcal after lunch);MED session: 250 kcal dietary deficit (−125 kcal at breakfast and −125 kcal at lunch) and a 250 kcal deficit induced by exercise (−125 kcal after breakfast and −125 kcal after lunch).

During the DED and MED sessions, the food intakes will be replicated identically to the CTL session, while the portion sizes will be adapted to induce the desired energy deficit (i.e., the same standard food items with reduced amounts). During the EED and MED sessions, two exercise bouts will be performed on a cycle ergometer at the target HR corresponding to 75% VO_2peak_ at the same time (after breakfast and lunch, respectively). The only difference between the EED and MED sessions is a modification of the exercise intensity to induce the desired energy expenditure.

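### Counterbalancing of the three deficit sessions is stated but no mechanism is described, and the ANOVA has no period term, so any week-to-week change in sleep enters the error or the realised contrasts

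*Protocol article*

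**What the plan says.** **Order.** Protocol article, section 2.3.1: "random permutations of interventions will be computed. Thus, each subject can be allocated to a specific order of interventions", and a participant may receive "any combination of EED, MED, or DED". Three sessions give six possible orders. No block, Latin square or equal use of the six orders is described. Section 2.5.2, referring back to this text, says that the "order will be randomized and counterbalanced".

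**Timing.** Section 2.3.1: "Upon reception of the signed consent, the participants will be subjected to a random allocation through a computer-generated list". Section 2.2.3 also screens for sleep apnoea on "the polysomnographic recording of the habituation night (i.e., apnea/hypopnea index > 5 events/hour"), and the run-in week that contains PSG familiarisation follows consent (sections 2.1 and 2.4.1). Section 2.3.2 keeps investigators blind to allocation until the baseline assessments end.

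**Analysis.** Section 2.10.1: differences between the three deficit sessions "will be assessed using a repeated-measures ANOVA by comparing the three interventions as a within-subject factor". No period or sequence term is named. Each deficit session is also compared with the control session "to evaluate the effect of each intervention separately, using paired samples" *t*-tests. Section 2.1 puts the control session first for everyone, with a week between sessions.

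**The concern.** Order is randomised in a crossover because sleep may change from week to week for reasons unrelated to the intervention, such as getting used to the recorder, the imposed sleep window or the academic calendar. There are two standard protections: a list that places each intervention equally often in each week, and a period term in the model. The article asserts the first without saying how it is achieved, and its model omits the second.

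The protections are complementary. Balance alone removes drift from the mean differences but leaves it in the residual, so the test becomes conservative. Random order without balance leaves part of the drift in the mean differences of the list actually drawn. What is at stake is the power of the three-way comparison of sleep efficiency, the primary outcome, and how closely the estimates from this one list reflect the interventions.

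**Working it through.** **Inputs.** From section 2.2.1: N = 24, alpha = 0.05, f = 0.25, correlation 0.5, sphericity 1, four measures, 80% power. From section 2.10.1: three sessions compared. Assumed, because the documents give none: a linear drift of b between-subject SDs per week, with b from 0 to 0.5.

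**1. The plan's own figure.** For one group and m repeated measures, lambda = f² × N × m / (1 − rho), with m − 1 and (N − 1)(m − 1) degrees of freedom. With m = 4, lambda = 0.0625 × 24 × 4 / 0.5 = 12 on 3 and 69 df. Power is 81.7% at N = 24 and 79.7% at N = 23, so 24 is reproduced.

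**2. Starting point for the planned ANOVA.** It compares three sessions, so lambda = 0.0625 × 24 × 3 / 0.5 = 9 on 2 and 46 df, and power is 74.1% with no drift. The gap between four and three measures is a separate matter; 74.1% is simply the reference here. With a balanced list and a period term (2 and 44 df), power is 74.0%.

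**3. Balanced orders, no period term.** The drift adds (−b, 0, +b) within each participant, a sum of squares of 2b², or 48b² over 24 participants. All of it falls in the residual. The expected residual without drift is 46 × 0.5 = 23, so the error mean square becomes (23 + 48b²) / 46. The F ratio shrinks by that value divided by 0.5, so the critical value of 3.20 is in effect raised:

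| b | Error mean square | Effective threshold | Type I error | Power |
|---|---|---|---|---|
| 0 | 0.500 | 3.20 | 5.0% | 74% |
| 0.1 | 0.510 | 3.27 | 4.7% | 73% |
| 0.3 | 0.594 | 3.80 | 3.0% | 66% |
| 0.5 | 0.761 | 4.87 | 1.2% | 52% |

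**4. Unrestricted random orders, no period term.** For one participant, the positions of two interventions differ by ±1 in four of the six orders and by ±2 in two, so the variance is (4 × 1 + 2 × 4) / 6 = 2. Over 24 participants the difference in mean position has mean 0 and SD √(2/24) = 0.29 weeks; in 95% of lists it is at most 0.58 weeks. A drift of 0.3 then moves a pairwise contrast by up to 0.3 × 0.58 = 0.17 SD, and 0.5 by up to 0.29 SD. For scale, f = 0.25 over three equally spaced means is an extreme difference of 2 × 0.25 × √1.5 = 0.61 SD. The chance that unrestricted draws use every order exactly four times is 24! / (4!⁶ × 6²⁴) = 0.07%.

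**5. Simulation of both cases** (20,000 trials per cell, inputs as above):

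| b | List | Type I, no period | Power, no period | Power, with period |
|---|---|---|---|---|
| 0 | balanced | 5.0% | 75% | 74% |
| 0 | random | 4.9% | 74% | 72% |
| 0.1 | balanced | 4.5% | 74% | 75% |
| 0.1 | random | 4.9% | 74% | 73% |
| 0.3 | balanced | 2.8% | 66% | 74% |
| 0.3 | random | 4.9% | 67% | 73% |
| 0.5 | balanced | 1.0% | 52% | 74% |
| 0.5 | random | 4.9% | 55% | 72% |

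The simulation agrees with step 3 to within about one point. With the period term, type I error is 4.6-5.1% in every cell.

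**The case against.** **The list may well be balanced.** A reader might infer that orders are drawn as simple, unrestricted permutations and that counterbalancing is therefore not delivered. The article does not say that. Randomly permuted orders can be arranged in a balanced list, section 2.5.2 says the order is counterbalanced, and block details are often left to a fuller document. This stands: the supportable statement is that counterbalancing is asserted without a described mechanism. The 0.07% applies only to the unrestricted reading. The missing period term matters on either reading.

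**Allocation at consent may do no harm.** A reader might infer that apnoea exclusions after consent remove allocated sequences and spoil the comparison. Such an exclusion precedes every deficit session and is unrelated to the assigned order, so it can disturb balance but cannot bias the comparison. Section 2.3.2 already keeps investigators blind through baseline, and the article does not say whether vacated orders are reused. This also stands; timing is a precaution for keeping balance, not a fault in itself.

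**Validity is intact and the drift is unknown.** Under unrestricted random orders the three-way test keeps its 5% level and is unbiased over lists. At 0.1 SD per week almost nothing is lost. A drift of 0.3 SD per week amounts to 0.6 SD from first to third session, as large as the planned effect, and the run-in and control night should absorb some early adaptation. This limits the point to efficiency and chance imbalance. It does not remove it, because the protection is nearly free.

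**Conclusion.** The point holds in limited form. Section 2.10.1 fixes a model without period, and section 2.5.2 relies on a balancing step that section 2.3.1 does not describe. The loss depends on a drift the documents do not give: negligible up to about 0.1 SD per week, about 6 to 8 points of power at 0.3, and about 17 to 22 points at 0.5, comparing the model without and with a period term on the same type of list. With balanced orders the test also becomes conservative; with unrestricted orders its level holds, but the estimates from one list may be shifted. The figures assume a linear drift common to all participants, f = 0.25, correlation 0.5 and complete data from 24 men.

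The comparisons with the control session are outside this repair. Control is always first, so those paired tests mix intervention with order, and neither a balanced list nor a period term can separate the two.

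**What to change.** 1. **Model.** In section 2.10.1, analyse the three deficit sessions with a linear mixed model: session and period as fixed effects, participant as random. The cost is 2 of 46 error degrees of freedom. With no drift and a balanced list, power goes from 74.1% to 74.0%; with an unrestricted random list the loss is about 2 points.
2. **List.** In section 2.3.1, state that each of the six orders is used four times among the 24 participants (6 × 4 = 24), for example by blocks of six. This gives section 2.5.2 the mechanism it refers to and costs one setting in the list generator.
3. **Timing.** Assign an order only to participants who remain eligible after the habituation night, so that exclusions do not use up places in the balanced list. No order is needed earlier, because the control session precedes all three deficit sessions.
4. **Control comparisons.** State that steps 1 to 3 do not remove the order confounding in the comparisons with the control session, and interpret those comparisons accordingly.
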